#### Achievement of similarity of interventions for blinding {24b}

For post-randomisation interviews, participants are asked not to disclose their received intervention to the outcome assessor. After the interview appointment, the outcome assessor completes a set of questions to assess the extent to which blinding may have been compromised. No further procedures are in place to enhance similarity between interventions to facilitate blinding.

#### Procedure for unblinding if needed {24c}

N/A. There are no circumstances under which it is necessary to unblind the above-mentioned research staff.

## Methods: data collection, management, and analysis

### Data collection methods

#### Plans for assessment and collection of trial data {25a}

By default, self-report questionnaires are administered digitally and largely automatically through CASTOR EDC. Still, completing questionnaires in a research location and/or using pen-and-paper forms remains possible, if preferred. If participants opt for pen-and-paper forms, data is transferred manually by a research assistant into CASTOR EDC. The original forms are scanned, stored locally and compared to the transferred data in CASTOR EDC by a second research assistant to prevent erroneous answer logging. The STiP-5.1 and the Dutch Reading Test for Adults (DART) are administered by trained assessors either in person or through video call. Participant scores are logged during or directly after assessment in CASTOR EDC by the assessor. If, due to the waiting list, ten weeks or more pass between baseline measurement and the start of treatment, part of the primary instruments is readministered in a pre-treatment measurement (see Table 1). Likewise, the STiP-5.1 is readministered if 6 months have expired before the start of treatment. The original versions of all instruments used are either subject to copyright of the original authors or can be shared upon request.

#### Primary outcome measures

##### Semi-structured Interview for Personality Functioning DSM-5 (STiP-5.1)

The Semi-structured Interview for Personality Functioning DSM-5 (STiP-5.1) measures criterion A of the alternative model for personality disorders (AMPD), which pertains to the LPF consisting of self and interpersonal functioning [62]. Both self and interpersonal functioning domains can be divided into two facets and six subfacets. For self-functioning, a) Identity (i. uniqueness, ii. self-esteem, iii. emotions) and b) Self-direction (iv. goals, v. norms, vi. self-reflection) can be distinguished. Likewise, interpersonal functioning consists of c) Empathy (vii. understanding others, viii. perspectives, ix. impact) and d) Intimacy (x. connection, xi. closeness, xii. mutuality). Clinical impression of the respondent’s answers on the subfacet level enables interviewers to allot functioning scores ranging from 0 (Little to no impairment) to 4 (Extreme impairment) and to estimate aggregate scores on the facet, domain and total level, also ranging from 0 to 4. It takes 45 minutes on average to administer the interview. A total score between 0 and 48 is given to indicate the participant’s global level of personality functioning. The instrument’s internal consistency for the domain scores and total score is high (Self α = 0.94; Interpersonal α = 0.94; total α = 0.97) [62]. Furthermore, satisfactory interrater reliability and construct validity were found. However, no research has been conducted on the sensitivity to change of the measure. In the current study, assessors will be trained through (online) courses, booster classes, and supervision. Interrater reliability will be calculated for part of the readmissions, using a random selection of baseline-pretreatment assessment pairs.

##### Level of Personality Functioning Scale – Brief Form 2.0 (LPFS-BF 2.0)

Similar to the STiP-5.1, the Level of Personality Functioning Scale – Brief Form 2.0 (LPFS-BF 2.0) measures criterion A of the AMPD. Each item reflects a basic underlying impairment related to the 12 features of personality functioning according to Criterion A of the AMPD, such as identity, self-direction, intimacy, and relational functioning, resulting in a total questionnaire length of 12 items [60]. The LPFS-BF 2.0 offers a severity index for personality pathology, making it suitable for measuring treatment effects. Each item is scored on a scale from 1 (= “Very false or often false”) to 4 (= “Very true or often true”). Therefore, participants achieve a total score between 12 and 48, representing the severity of impairment in personality functioning. Weekers et al. [60] found that the scale possessed acceptable internal consistency (total scale α = 0.82; self-functioning subscale α = 0.79; interpersonal functioning subscale α = 0.71) and construct validity, as well as high sensitivity to change. Furthermore, this version of the LPFS is recommended by the International Consortium for Health Outcomes Measurement (ICHOM) as an outcome in personality disorder research [61].

#### Secondary outcome measures

##### Severity Indices of Personality Problems – Short Form (SIPP-SF)

The Severity Indices of Personality Problems – Short Form (SIPP-SF) is a dimensional self-report questionnaire measuring the severity of personality pathology by assessing the core components of adaptive and maladaptive personality functioning. This is captured in the five facets of self-control, identity integration, responsibility, relation capacities, and social concordance [63]. The questionnaire was designed in line with the concept of personality disorders as defined in the Alternative Model for Personality Disorders. In answering the 60 items, a 4-point Likert scale is used that ranges from 1 ( = fully disagree) to 4 ( = fully agree). The SIPP-SF has been shown to be sensitive to changes, in particular the facets of self-control, identity integration, and relational capacities. Furthermore, the instrument has excellent internal consistency (α = 0.75–0.91) and satisfactory validity [64].

##### Structured Clinical Interview for DSM-5 Personality Questionnaire (SCID-5-PQ)

The SCID-5-PQ is the self-report screener that belongs to the Structured Clinical Interview for DSM-5 Personality Disorders (SCID-5-PD) [65]. The questionnaire uses 106 yes/no items to screen all symptoms of the categorical personality disorder diagnoses. The screener tends to elicit many false positives and few false negatives, making it unsuitable as a stand-alone instrument in classifying personality disorders. Hence, in the current study, the questionnaire is solely used to track subjective symptom change as operationalised in Section II of the DSM-5-TR [66].

##### Brief Symptom Inventory (BSI)

The Brief Symptom Inventory (BSI) consists of 53 items, which are answered using a Likert scale comprising five levels (0–4; “Not at all” to “Extremely”). This questionnaire was developed for clinical settings and measures distress and typical psychopathological symptomatology, including somatisation, obsessive-compulsivity, interpersonal sensitivity, depression, anxiety, hostility, phobic anxiety, paranoid ideation, and psychoticism [67]. A global severity index and subscores on all 9 domains are calculated by summing the values on all items and dividing by the number of items. De Beurs & Zitman [68] showed the scale has excellent internal consistency for the Global Severity Index (GSI; α = 0.96). The subscales’ internal consistency ranges from acceptable to good (α = 0.71–0.87), while having a modest sum of items per scale. Test-retest reliability over a short period is promising (GSI *r* = 0.90, subscales *r* = 0.71–0.89). An adequate sensitivity for measuring therapeutic change has been recorded simultaneously. Moreover, the BSI has satisfactory convergent and divergent validity.

##### Columbia – Suicide Severity Rating Scale Screener/Recent Self-Report (C-SSRS)

The Columbia – Suicide Severity Rating Scale Screener/Recent Self-report (C-SSRS), developed by Posner et al. [69], assesses suicidal ideation using six items. The instrument exhibits excellent internal consistency (ordinal α = 0.98) and satisfactory construct validity (predictive and concurrent) [70, 71]. Also, this version of the C-SSRS is recommended by ICHOM as an outcome in personality disorder research [61].

##### Who Disability Assessment Schedule (WHODAS 2.0)

The 12-item WHO Disability Assessment Schedule (WHODAS 2.0) aims to measure the level of functioning on six domains: cognition, mobility, self-care, getting along, life activities, and participation. Respondents use a 5-level Likert scale to disclose how much difficulty they experience in the above-mentioned domains, ranging from “None” to “Extreme or cannot do” [72]. Saltychev et al. [73] systematically reviewed the psychometric properties of the WHODAS 2.0 in a diversity of samples and found the internal consistency to range from *α* = 0.82 to *α* = 0.95, which can be interpreted as good to excellent. Axelsson et al. [74] demonstrated good test-retest reliability (*r* = 0.83) and good construct validity. Additionally, the WHODAS 2.0 is part of the standard tool set advised by ICHOM for research on personality disorders [61].

##### Quality of Life (EQ-5D-5 L)

The EQ-5D-5 L measures decrements in health using five dimensions (mobility, self-care, usual activities, pain/discomfort, anxiety/depression), answered through a 5-point Likert scale ranging from “no problems” to “unable to” [75]. In their review, Feng et al. [76] found satisfactory test-rest reliability at the index level. Moreover, the authors conclude that the questionnaire possessed acceptable convergent and known-groups validity.

##### Quality of Life Enjoyment and Satisfaction Questionnaire – Short Form (Q-LES-Q-SF)

The Quality of Life Enjoyment and Satisfaction Questionnaire – Short Form (Q-LES-Q-SF) covers 16 items, which are answered in a 5-point Likert scale (“not at all or never” to “frequently or all the time”), to assess quality of life in the domains of physical health, subjective feelings, leisure activities, satisfaction with medication, and overall life satisfaction [77]. The short variant was extracted from the original 93-item Q-LES-Q by Endicott et al. [78]. The Q-LES-Q-SF has excellent internal consistency (*α* = 0.90) and test-retest reliability (*r* = 0.93) [77]. Furthermore, the scale has demonstrated strong convergent and discriminant validity [79].

##### Treatment Inventory of Costs in Patients with Psychiatric Disorders (TiC-P)

The Treatment Inventory of Costs in Patients with Psychiatric disorders (TiC-P) assesses healthcare consumption and productivity loss using 57 items, enabling the economic evaluation of mental illness and healthcare [80, 81]. Bouwmans et al. [80] showed satisfactory construct validity and test-rest reliability in estimating healthcare use of different provider groups (*ICC* two-way mixed models, absolute agreement = 0.57–0.88), except for the alternative medicine dimension (ICC = 0.231).

#### Predictors

The aforementioned secondary instruments assessed at baseline will also serve as candidate predictors in the PAI analysis. These candidate predictors have been selected based on previously identified predictors in comparable analyses [45, 82], as well as alignment with variables examined in ongoing or upcoming trials on optimal treatment selection for personality disorders [83–86]. Moreover, their inclusion allows for replication and verification of related findings, enhancing the robustness of predictor research surrounding PD.

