#### Secondary objectives

The secondary objectives are, first, to assess whether generalist treatment (GIT-PD) is non-inferior (*d* ≥ − 0.25) to specialist treatment (MBT/ST) in improving general symptom severity and psychosocial functioning in participants with severe personality disorders from baseline to the end of treatment (18 months; T4). Second, to evaluate whether generalist treatment (GIT-PD) is non-inferior to specialist treatment (MBT/ST) in participants with severe personality disorders in maintaining improvements observed at 18 months in personality functioning, general symptom severity, and psychosocial functioning from baseline to 12-month follow-up (30 months; T6). Third, to determine whether generalist treatment (GIT-PD) is more cost-effective than specialist treatment (MBT/ST) in terms of improvements in personality functioning for participants with severe personality disorders. Fourth, to explore the extent to which an algorithmically optimised combination of demographic, clinical, and psychosocial variables can predict differential treatment response (as measured by change in level of personality functioning (LPF) between baseline and end of treatment) between generalist (GIT-PD) and specialist (MBT/ST) treatments, with the expectation that combining predictors in one algorithm will outperform chance-level prediction.

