### Outcomes {16}

The first primary outcome is the mean difference in change from baseline to end of treatment (T4) in clinician-rated personality functioning between the generalist (GIT-PD) and specialist treatment (MBT/ST) conditions, as assessed with the clinical STiP-5.1 interview. Furthermore, the second primary outcome refers to the mean difference in change from baseline to end of treatment (T4) in self-reported personality functioning between the generalist (GIT-PD) and specialist treatment (MBT/ST) conditions, based on the Level of Personality Functioning Scale – Brief Form 2.0 (LPFS-BF 2.0) questionnaire. Inclusion of the STiP-5.1 interview measure allows for blinded, clinician-rated outcome assessment, which reduces potential bias [58]. Moreover, interview measures capture a larger proportion of the variance of a latent general PD severity than self-reported questionnaires [59]. However, the use of the STiP-5.1 in psychotherapy research is novel, leading to little knowledge on the measure’s sensitivity to change [53]. Concurrently, the self-reported LPFS-BF 2.0 questionnaire has demonstrated high sensitivity to change, while its use is more established in international research [60, 61]. Therefore, the STiP-5.1 interview is given priority regarding the primary outcome, but supplemented with the self-reported LPFS-BF 2.0 questionnaire.

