The secondary outcomes, among others, include the mean differences in change from baseline to the end of treatment (T4) in symptom severity (SIPP-SF, SCID-5-PQ, BSI, C-SSRS; for an outline of the here-abbreviated outcome measures, see *Plans for assessment and collection of trial data {25a})* and psychosocial functioning (WHODAS 2.0, EQ-5D-5 L, Q-LES-Q-SF) between the generalist (GIT-PD) and specialist treatment (MBT/ST) conditions. Additional secondary outcomes assess the mean differences in change from baseline to follow-up (T6) between the generalist (GIT-PD) and specialist treatment (MBT/ST) conditions in personality functioning (STiP-5.1, LPFS-BF 2.0), symptom severity (SIPP-SF, SCID-5-PQ, BSI, C-SSRS), and psychosocial functioning (WHODAS 2.0, EQ-5D-5 L, Q-LES-Q-SF). For both the short- and long-term outcomes, all available measurement points are included in the model. The secondary outcome surrounding cost-effectiveness and cost-utility of generalist (GIT-PD) versus specialist treatment (MBT/ST) addresses the incremental effects set off against the incremental costs from baseline to end of treatment (T4), calculating an incremental cost-effectiveness ratio (ICER). For the cost-effectiveness analysis, improvement in personality functioning (STiP-5.1, LPFS-BF 2.0) is set off against the incremental costs, referring to direct and indirect costs, such as treatment costs (electronic patient file data), further healthcare consumption and productivity loss (TiC-P). All the while, cost-utility is measured in quality-adjusted life years (QALYs) gained throughout the assigned intervention, calculated from EQ-5D-5L scores. The final secondary outcome measures the combined predictive value of end-of-treatment differential treatment response, based on several pre-randomisation variables. The predictive value is expressed in a personal advantage score in terms of LPF improvement from baseline (STiP-5.1, LPFS-BF 2.0). The pre-randomisation variables with prescriptive and/or prognostic value are selected and used for predicting advantage scores through the development of a PAI algorithm. For a detailed description of the instruments and the timeline of assessment, see *Plans for assessment and collection of outcomes {25a}* and *Participant timeline {18}*.

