##### Demographic and Clinical Characteristics

At baseline, participants answer questions regarding their biological sex, identified gender, age, ethnicity, education level, (potential) custody of children, marital and relationship status, sexual orientation, living situation, religion, employment, net income, income source(s), and the number of prior therapies received for which complaints, and within which theoretical framework. Any DSM classifications the participant has been diagnosed with at intake by the participating institution are retrieved from their electronic patient file.

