Subsequently, distinct prediction models are to be fitted for the generalist and specialist treatment. First, predictors will be selected using Elastic Net regression, which is a supervised machine-learning method that combines the penalised linear Lasso and Ridge regressions to identify a parsimonious and stable subset of predictors. Then, Ridge regression will be used to fit the final prediction models using the selected predictors per treatment. For the participants in the test-fold of the 5-fold cross-validation, the resulting prediction models will be used to calculate a ‘factual’ prediction for the treatment actually received and a ‘counterfactual’ prediction for the treatment not actually received. To quantify the performance of the prediction models for both treatments, the outcome of the factual prediction will be compared to the actual LPF at post-treatment in terms of the mean absolute error (MAE), the root mean square error (RMSE), and the correlation.

The PAI scores are then derived from subtracting the counterfactual prediction from the factual prediction to discern whether a participant received their optimal or non-optimal treatment. Negative and positive PAI scores refer to having received the optimal and nonoptimal treatment, respectively. The PAIs utility in guiding treatment selection will be evaluated through comparing LPF at post-treatment for participants having received their optimal versus nonoptimal treatment using an independent one-sided t-test. Additionally, Cohen’s *d* will be computed for the mean difference. As per customary practice in PAI analyses, this evaluation should be repeated for the 50% of participants with the largest absolute PAI scores to determine utility for those with the strongest predictions. The Advanced PAI approach will be performed for both the clinician-rated (STiP-5.1) and the self-reported LPF (LPFS-BF 2.0).

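### The PAI candidate predictors leave out baseline STiP-5.1 and LPFS-BF 2.0 although the algorithm predicts post-treatment personality functioning, and the PAI outcome is defined in two ways

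*Protocol article*

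**What the plan says.** The Predictors section of the protocol article builds the candidate list in two parts. The first is the set of secondary outcome instruments: "The aforementioned secondary instruments assessed at baseline will also serve as candidate predictors in the PAI analysis". The second, under the same heading, is demographic and clinical information ("At baseline, participants answer questions regarding their biological sex, identified gender, age, ethnicity", and so on, with diagnoses from the patient file) plus 13 dedicated instruments, from the CTQ-SF to the PID-5-SF.

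STiP-5.1 and LPFS-BF 2.0 are described under Primary outcome measures, and Outcomes {16} treats them as such: "Therefore, the STiP-5.1 interview is given priority regarding the primary outcome, but supplemented with the self-reported LPFS-BF 2.0 questionnaire". They are therefore not among the secondary instruments, and the Predictors section does not name them.

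The target of the prediction is given differently in different places:
- Statistical methods {27a} uses the level at post-treatment: "the outcome of the factual prediction will be compared to the actual LPF at post-treatment". The same section compares post-treatment LPF between participants who received their optimal and their nonoptimal treatment, by t-test, with no baseline term stated.
- Secondary objectives describes the response "as measured by change in level of personality functioning (LPF) between baseline and end of treatment".
- Outcomes {16} says: "The predictive value is expressed in a personal advantage score in terms of LPF improvement from baseline (STiP-5.1, LPFS-BF 2.0".

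The labelling rule in {27a} is: "Negative and positive PAI scores refer to having received the optimal and nonoptimal treatment, respectively".

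**The concern.** A model for a post-treatment score normally has that score's own baseline value among its predictors. The rest of the article points the same way. The Background lists personality functioning among characteristics earlier suggested as predictors of response, and the non-inferiority models in {27a} adjust for the baseline value of the outcome. Both baseline scores are available before randomisation, and STiP-5.1 is needed for eligibility.

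At stake is the third main question of the trial, which patient characteristics predict a different outcome under generalist and specialist care. If the list is followed as written, the arm-specific models lose accuracy on the measures the article will report (MAE, RMSE, correlation). Baseline LPF also cannot be tested directly as a moderator. The two outcome definitions leave it open which variable is modelled and how the sign of the PAI is to be read.

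**Working it through.** **1. Where each instrument sits.** Primary outcome measures: STiP-5.1, LPFS-BF 2.0. Secondary outcome measures: SIPP-SF, SCID-5-PQ, BSI, C-SSRS, WHODAS 2.0, EQ-5D-5L, Q-LES-Q-SF, TiC-P. Predictors: demographic and clinical characteristics and 13 further instruments. The candidate list is the second and third groups; the first appears in neither.

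**2. The input r = 0.50.** The article gives no performance figure for the PAI. The one usable input is the repeated-measures correlation of 0.50 in Sample size {19}, so I first checked that it fits the stated sample size.
- Attrition: 316/0.883 = 357.87, hence 358, as stated.
- Linear growth model, seven equally spaced measures: variance of the first-to-last difference = (1 − 0.50) × 6²/28 = 0.643. Per group, n = 2 × (1.960 + 0.842)² × 0.643/0.25² = 162, so 324 in total, within 3% of 316. Spacing by the actual months gives 302.

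The correlation is consistent with the stated figure.

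**3. Variance explained by the omitted score.** R² = r² = 0.50² = 0.25, and the residual SD is √(1 − 0.25) = 0.87 instead of 1.00. Suppose a listed proxy correlates c with the baseline score and relates to the outcome only through it. The proxy then recovers 0.25c², and the loss is 0.25(1 − c²). The value of c is an assumption; the article gives none.

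| c (assumed) | R² recovered by proxy | R² lost |
|---|---|---|
| 0 | 0 | 0.25 |
| 0.5 | 0.06 | 0.19 |
| 0.7 | 0.12 | 0.13 |
| 0.8 | 0.16 | 0.09 |

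**4. Effect on the reported performance measures.** Illustrative simulation: n = 316, 20 predictors, separate ridge models per arm, 5-fold cross-validation, 300 runs. Baseline is equally prognostic in both arms (slope 0.5), and five other predictors are the moderators. It simplifies the planned procedure: one cross-validation split per dataset and no Elastic Net step.

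| c | RMSE without → with baseline | Correlation without → with | Optimal vs nonoptimal d without → with |
|---|---|---|---|
| 0 | 1.02 → 0.88 | 0.13 → 0.47 | 0.29 → 0.32 |
| 0.5 | 0.99 → 0.88 | 0.23 → 0.47 | 0.28 → 0.30 |
| 0.8 | 0.93 → 0.88 | 0.37 → 0.47 | 0.29 → 0.31 |

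Predictive accuracy improves clearly; the treatment-advantage contrast hardly moves.

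**5. Effect on recommendations.** This depends on an unknown. If baseline LPF is assumed to be the moderator (arm slopes 0.3 and 0.7), correct recommendations are 57% to 67% without it, for c from 0.5 to 0.8, and 77% with it. If it is equally prognostic in both arms (0.5 and 0.5) and another listed variable moderates, they are 75% to 76% without and 76% with; under weaker moderation, 65% and 66%.

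**6. Would modelling change remove the problem?** No. With equal SDs and r = 0.50, the covariance of baseline with (post − baseline) is 0.50 − 1 = −0.50, and the variance of the change is 1 + 1 − 2 × 0.50 = 1. Baseline therefore correlates −0.50 with change and explains 25% of that too.

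**7. The sign rule.** PAI = factual − counterfactual prediction. On both instruments a higher score means more impairment, so a negative PAI marks the better treatment when the post-treatment level is modelled. The same holds for change coded as post minus baseline. It would not hold for a gain coded as baseline minus post.

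**The case against.** The strongest reply is that the omission is inferred from silence. The list is not called exhaustive, and Outcomes {16} describes the pool in general terms: "The pre-randomisation variables with prescriptive and/or prognostic value are selected and used for predicting advantage scores". That wording would admit baseline LPF. Table 1 is not shown, and part of the analysis plan lies in a registry protocol that is not at hand. Against this, the administrative table says the statistical analysis plan is available in this publication, and the Predictors section is itemised by instrument. General wording does not put two named scores on that list. The reply lowers certainty about intent but does not remove the need to say so.

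Several stronger readings are tempting, and the documents do not support them:
- **That only secondary instruments are candidates.** They will also serve, next to demographics, diagnoses and 13 scales.
- **That the PAI could not detect moderation by severity.** The SIPP-SF is a candidate and is described as measuring severity of personality pathology in line with the AMPD; the SCID-5-PQ and PID-5-SF may overlap as well. These are all self-report, however, whereas the article holds that interviews capture more of latent severity, so they stand in less well for STiP-5.1.
- **That many treatment recommendations would be wrong.** The large difference in step 5 follows from assumed slopes that no section gives.
- **That the optimal and nonoptimal labels are reversed.** This needs improvement coded as baseline minus post with the rule left unaltered, and no section states that coding.
- **That baseline LPF is the main prognostic variable.** The article does not rank predictors. Entry on severe STiP-5.1 scores may narrow the baseline range and bring r for that scale below 0.50, and the 25% falls with the square of r.

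**Conclusion.** The point holds in a limited form. Read as written, the candidate list omits the baseline value of the outcome being predicted. At r = 0.50 this costs up to 25 points of R², or about 9 to 19 points if a listed proxy correlates 0.8 to 0.5 with it. The loss falls on predictive accuracy, and baseline LPF can be tested as a moderator only indirectly. No loss in treatment selection is demonstrated; it would arise only if baseline LPF does moderate response. The mismatch between change (Secondary objectives, Outcomes {16}) and post-treatment level ({27a}) is real, but as a matter of definition rather than a shown reversal of results.

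The size rests on the sample-size correlation applying to both instruments from baseline to 18 months, and on assumed proxy correlations. The PAI is an exploratory secondary aim.

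**What to change.** - **Predictors:** add the pre-randomisation (T0b) STiP-5.1 and LPFS-BF 2.0 scores to the candidate predictors.
- **Optionally,** always retain the baseline value of the outcome being predicted in both arm-specific models. The collinearity screen in {27a} drops one of any two candidates correlated above 0.75, and the Elastic Net may also deselect it, so candidacy alone does not guarantee that it stays. Retention departs from pure data-driven selection and is the authors' choice.
- **Secondary objectives and Outcomes {16}:** define the PAI outcome as post-treatment LPF with baseline among the predictors, to match {27a}.
- **{27a}:** state beside the labelling rule that higher scores are worse on both instruments.

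The cost is wording in an amendment and two more candidates. Both scores are already collected, so no new assessment is needed. Fixing this before outcome data are analysed also avoids a post hoc choice of predictors or outcome.
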